### Analysis of experience of care

The analysis of patient satisfaction with care and perceived continuity of care measured through quantitative methods will follow similar procedures to those described in the ‘analysis of clinical and social outcomes’ paragraph.

Data from semistructured interviews with patients and clinicians will be audio taped and transcribed verbatim, ensuring the removal of any identifying information to maintain anonymity. Transcripts will be analysed through a thematic content analysis method.^42^ Study centres in each country will generate a list of emerging codes based on a line-by-line analysis of the first three interviews with patients and first two with clinicians in the respective country.^43^ Consistency of coding will be assessed across all centres. First, researchers at the Institute of Psychiatry and Neurology of Warsaw (IPIN) and at Queen Mary University of London (QMUL) will screen the databases containing the coding results of the first interviews in each centre and discuss any discrepancies with the relevant centre. Second, researchers from all centres will provide further verification and clarification of the meanings of the codes during a one-day workshop. Third, each partner will code two interviews with patients and two interviews with clinicians (conducted in English or translated into English), and researchers at IPIN and QMUL will assess the coded data for discrepancies. Separate codebooks will be developed for interviews with patients and with clinicians, and interviews will be coded based on these.

Codes will be categorised based on their English translations. To obtain meaningful themes, the emerging categories and codes will be organised and grouped. Researchers from all centres will verify the emerging categories and themes to ensure consistency across the data set. Descriptive counts of themes, categories and codes will be use to summarise the data set.

QMUL group is experienced in conducting qualitative analyses of data from different countries as they have already led previous similar studies in which IPIN was also involved.^44^
^45^

### Secondary analysis based on continuity of care as a ‘continuum’

A wide variability of care arrangements may support specialisation of clinicians and teams or personal continuity of care. This may determine intragroup differences among the services included within the categories of ‘specialisation’ and ‘personal continuity’ of care approaches. For example, the presence of a ‘care coordinator’ may guarantee continuity of care even when there are two different primary clinicians in the hospital and in the community. On the other hand, even when patients have the same primary clinician in the hospital and in the community, they may be treated for short periods of time by ‘specialist services’ such as home-treatment teams, emergency wards or psychiatric intensive care units led by different primary clinicians.

We will investigate the variety of system characteristics that lead to the implementation of specialisation and personal continuity of care in the five participating countries. This part of the study will focus on the financial and healthcare governance mechanisms that support both care approaches and will be led by the University of Louvain.

To explore this in more depth, we will also develop an instrument assessing continuity of care as a continuum. We will use this instrument to identify and rate different care arrangements within the two alternative approaches.

The association between different levels of continuity of care and the outcomes will be tested through mixed models taking into account random effects at an hospital level and fixed effects of the same covariates described above for the primary analysis.

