### Procedures

#### Establishing exposure to ‘specialisation’ or ‘continuity’ of care approach

To reflect differences in how mental healthcare services operate in the five countries, different procedures are used to ascertain exposure status to either a ‘specialisation’ or ‘personal continuity’ of care approach.

In the UK and in Italy, all patients admitted to the same hospital are treated under the same care approach, either a ‘specialisation’ or ‘personal continuity’ approach. In these countries, the local providers of care, that is, an ‘NHS Trust’ in UK and a ‘Dipartimento di salute mentale’ in Italy, may follow either the ‘specialisation’ or ‘personal continuity’ of care approach. The care is organised in the same way for all patients treated by the same provider of care which operates in a specific geographic area.

In Belgium, Germany and Poland, patients admitted to the same hospital can be treated under either a ‘specialisation’ or a ‘personal continuity’ of care approach. This is determined by patients’ health insurance arrangements (Germany) and/or by a mental health team decision in which the patient may or may not be involved (Belgium, Poland and Germany). Therefore, a patient is included in either group based on the primary hospital clinician report at discharge in Belgium, Poland and Germany.

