### Sample size determination

The sample size for the quantitative study was calculated with the aim to detect a 5% difference in rates of re-admissions (ie proportion of patients re-hospitalised during the one year follow up) between the two care approaches from 27.5% to 32.5% with 80% power at the 5% significance level.

The sample size required for an individual-level comparison not considering clustering of outcomes within centres and hospital would be 2716 patients.

We calculated an average cluster size per hospital of 150 patients recruited over one year. Taking into account a 15% drop out rate, the average number per hospital of patients recruited and followed up will be 128. The variance inflation factor (or design effect, IF) is given by IF=1+(m−1)×ρ; where m=cluster size, and ρ=ICC (inter-cluster correlation coefficient). The ICC in a cluster with such a large number of patients is expected to be very small.^37^ With m=128 and ρ=0.007, IF is 1.90, and the adjusted sample size is N=5162 (1034 per country), requiring eight hospitals per country with an average number of 150 patients recruited per hospital, ie 1200 patients per country and 6000 overall.

We will carry out follow-up face-to-face interviews with a subsample of patients who will be 18–65 years of age. The patients will be stratified based on diagnostic group (ICD codes: F20–29, F30–39, F40–49)^27^ and on whether the index admission was their first one or they have had previous hospital admissions. We will aim to interview 30 patients per stratum, resulting in 360 patients per country (60×6 clusters) and an overall sample of 1800 patients (360×5 countries).

For the in-depth interviews, we will purposively select 40 patients and 13 clinicians in each country, resulting in a total sample of 200 patients and 65 clinicians.

Within the sample, there will be a mix of: (1) patients treated with ‘specialisation’ and ‘personal continuity’ of care approaches; (2) those who were rehospitalised during the follow-up and those who were not; and (3) patients with different diagnoses (F20–29, F30–39, F40–49).

Clinicians will be included taking into account: (1) the care approach (‘specialisation’ or ‘personal continuity’) adopted by the service they work within and (2) their qualification: psychiatrists, psychologists, nurses/social workers.

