### Analysis of clinical and social outcomes

Mixed effects models with an unstructured variance matrix will be used to assess differences in the primary outcome (rehospitalisation), and in the other clinical and social outcomes between the two groups. We will explore random effects for the hospitals or ‘specialisation’ and ‘personal continuity’ of care clusters within the hospital (in Germany, Belgium and Poland), and use fixed effects for the following covariates:
Age, gender, diagnostic group, whether or not a patient has been previously admitted, severity of illness at baseline, social situation (SIX score) and formal status of the patient at baseline.

We will check the selection bias by comparing data of our sample with the aggregate data for the total group of admitted patients during the same period.

Potential mediators of effectiveness may be: (1) the intensity of treatment, that is, sum of inpatient days and outpatient visits; (2) the experience of hospital care within the index admission, which has been shown to be predictive of better outcomes following discharge.^38^
^39^ A higher intensity of treatment or a better experience of hospital care may occur in either the ‘specialisation’ or the ‘personal continuity’ of care approach and be responsible for better outcomes.^21^
^38^ We will develop a mediation model^40^ in order to identify and explicate a potential effect of intensity of treatment and/or experience of hospital care during the index admission for assessing the effectiveness of the two approaches.^41^

Exploratory analyses to compare clinical outcomes, social outcomes and untoward events between the ‘specialisation’ and ‘personal continuity’ of care approaches will also be carried out on subgroups of patients defined by:
Age (younger or older than 40 years);Gender (males or females);Primary psychiatric diagnosis (F20–29 or F30–39 or F40–49);First or repeated admission;Socioeconomic situation (receiving state benefits due to low income or not);Migrant status (ie, country of residence different from country of birth or not);Presence of physical comorbidity/comorbidities for substance use, diabetes, cardiovascular diseases or not.

All subgroup analyses will be performed by including the relevant variables as interaction terms in the models.

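### The continuity-continuum model has a random effect for hospital only, although in Belgium, Germany and Poland one hospital can hold several differently scored care arrangements; the standard error of the gradient is then modestly too small if arrangements differ in outcome

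*Protocol article*

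**What the plan says.** All references are to the protocol article.

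- **Unit that is scored.** The section on the secondary analysis of continuity as a continuum announces a new instrument and states: "We will use this instrument to identify and rate different care arrangements within the two alternative approaches".
- **Model for the score.** The same section says that the association between continuity level and outcomes "will be tested through mixed models taking into account random effects at an hospital level". From the primary analysis it imports only the fixed-effect covariates.
- **Where exposure varies.** The section on establishing exposure says "In Belgium, Germany and Poland, patients admitted to the same hospital can be treated under either a" specialisation or a personal-continuity approach. The Settings section agrees. For the other two countries: "In the UK and in Italy, all patients admitted to the same hospital are treated under the same care approach".
- **Primary model.** Analysis of clinical and social outcomes offers random effects for hospitals or for specialisation and personal continuity "of care clusters within the hospital (in Germany, Belgium and Poland"). This is a finer level than the continuum section names.

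**The concern.** A mixed model protects the standard error of an exposure effect only if it carries variance at the level where the exposure is assigned. Here that level is the care arrangement. If a hospital contains two arrangements with different scores, part of the gradient is estimated from the contrast between them. A hospital intercept cancels out of that contrast. Any outcome difference between the arrangements that is unrelated to continuity (staff, thresholds for admission, unmeasured case mix) is then set against patient-level noise alone. In these three countries the approach follows insurance, team decisions or patient choice, so shared case mix within an arrangement is plausible.

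At stake is the reliability of the graded association between continuity and outcome: intervals somewhat too narrow, and a test that rejects somewhat too often, in a study meant to feed policy recommendations.

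**Working it through.** **1. The plan's own figures.** The article gives no figure for the continuum analysis. The sample-size section supplies the cluster size and the correlation, so I checked that section first.

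- Rates "from 27.5% to 32.5% with 80% power at the 5% significance level", taken as two-sided with equal groups: n per group = [1.96·√(2·0.30·0.70) + 0.8416·√(0.275·0.725 + 0.325·0.675)]² / 0.05² = 1318. With the continuity correction it is 1358, so 2 × 1358 = 2716, as stated.
- Design effect: 1 + (128 − 1) × 0.007 = 1.889, stated as 1.90. 2716 × 1.90 = 5160, against 5162 stated.

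I therefore use 128 followed patients per hospital, eight hospitals per country and a correlation of 0.007.

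**2. The mechanism in one hospital.** Assume two arrangements of 64 patients and total variance 1. Let *u* be the hospital share and *v* the arrangement-within-hospital share.

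- True variance of an arrangement mean around its hospital: v + (1 − u − v)/64.
- Variance used by a hospital-only model: (1 − w)/64, where w is the average correlation between two patients of the hospital. The proportion of pairs in the same arrangement is 2·64·63/(128·127) = 0.496, so w = u + 0.496·v.
- With u = 0 and v = 0.007: true 0.007 + 0.993/64 = 0.02252; w = 0.00347; model 0.99653/64 = 0.01557. The standard-error ratio for the within-hospital contrast is √(0.02252/0.01557) = 1.20.
- Hospital means are handled correctly: true v/2 + (1 − v)/128 = 0.01126, model w + (1 − w)/128 = 0.01126.

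The loss sits wholly in the within-hospital part. A gradient that also uses differences between hospitals is affected less.

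**3. The whole gradient.** I compared the true (sandwich) standard error of the slope with the one reported by a hospital-only model. Assumptions: 24 hospitals in Belgium, Germany and Poland with two or four equal arrangements each; 16 hospitals in the UK and Italy with one each; independent normal scores; a linear approximation to the binary outcome. Actual alpha = 2·[1 − Φ(1.96/ratio)].

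| Hospital share u | Arrangement share v | Two per hospital, all countries | Two per hospital, BE/DE/PL only | Four per hospital, all countries |
|---|---|---|---|---|
| 0.007 | 0 | 1.00 (5.0%) | 1.00 (5.0%) | 1.00 (5.0%) |
| 0.0035 | 0.0035 | 1.06 (6.3%) | 1.07 (6.7%) | 1.05 (6.1%) |
| 0 | 0.007 | 1.10 (7.6%) | 1.13 (8.3%) | 1.09 (7.2%) |
| 0.007 | 0.007 | 1.12 (8.0%) | 1.15 (8.9%) | 1.09 (7.1%) |
| 0.007 | 0.02 | 1.35 (14.8%) | 1.42 (16.7%) | 1.23 (11.2%) |

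Rows two and three keep the total at the plan's 0.007. The last two rows exceed it.

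**The case against.** **The wording may be shorthand.** The article uses a hospital-level random effect as a general description in several places (Study design, the Discussion on methodology, Potential challenges), so the continuum sentence might mean the fuller structure of the primary model. This is possible. But the sentence carries over only the covariates and names its random-effect level separately. Read as written, it leaves out the within-hospital term. Because a level is stated, the point is not a detail left to the analysis plan.

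**The scored unit is not final.** The instrument is still to be developed. If the score turns out constant within a hospital, the stated model is adequate. If it is patient-specific, the shared-score argument largely falls away. That stands, and makes the point conditional. The text does, however, say that arrangements are what will be rated.

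**Tempting stronger readings.** A reader might infer that all patients sharing a score are treated as independent throughout the study. The article does not support this. The hospital intercept covers the clustering wherever one arrangement fills a hospital. For the UK and Italy it states "The care is organised in the same way for all patients treated by the same provider of care", which points that way. In the other three countries the intercept still captures part of the clustering. A reader might also infer that the standard error is certainly and seriously too small. No arrangement-level variance is given anywhere, and at zero variance nothing is lost. The rejection rates above 10% need an assumed correlation of 0.02, nearly three times the plan's whole value. Nor do the documents say that every hospital in the three countries holds several arrangements, only that this can happen.

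**Conclusion.** The point holds in a limited form. The continuum model names a coarser random effect than the unit it scores, and it omits a term that the article itself offers the primary model in Belgium, Germany and Poland. The standard error is understated if two conditions hold: scores differ within a hospital, and outcomes vary between its arrangements beyond what continuity explains. At the plan's correlation of 0.007 the understatement is a factor of about 1.05 to 1.10 over all countries, or an actual alpha of about 6% to 8%. At an assumed 0.02 the factor is about 1.23 to 1.35. These sizes rest on the assumed layout, scores and variance split; only the direction follows from the model. The analysis is secondary, and neither the sample size nor the primary comparison is affected.

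**What to change.** In the section on the secondary analysis of continuity as a continuum, name the unit that receives a continuity score. Replace the hospital-only statement with the random-effect structure of the primary model, taken to that unit: a random intercept for each scored unit, nested in hospital, wherever a hospital contains more than one. Where a hospital has a single scored unit the two terms cannot be separated, and the hospital intercept alone should be kept. An approach-by-hospital term may be too coarse, because the instrument is meant to separate arrangements within an approach.

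The cost is one extra variance term and somewhat wider intervals in a secondary analysis. If the arrangement variance is nil, inference is essentially unchanged.

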## Discussion

COFI is a natural experiment which will overcome limitations of the currently available evidence:
It is a multicentre study carried out in countries with very different traditions, funding mechanisms and policies for mental healthcare. In all these countries, care approaches supporting either specialisation or personal continuity of care coexist. This will allow for comparisons to be made within a similar context and not be confounded by country-specific characteristics. The service arrangements supporting specialisation or personal continuity of care may vary substantially among the countries, which will make our findings more robust and increase their generalisability to other countries and contexts.It is powered to detect very small differences in clinical and social outcomes between the two care approaches assessed that are relevant from a policy decision-making point of view (eg, 5% in rates of rehospitalisation).A comprehensive range of outcomes will be assessed, encompassing clinical outcomes, social outcomes, safety of care indicators, patient satisfaction with services and cost-effectiveness.Care approaches supporting specialisation or personal continuity of care which are assessed in this study are already established as routine services and are not just pilot experimental services. This will be a methodological safeguard from the ‘novelty bias’ found in the existing literature in which the newly established approaches (either supporting specialisation or continuity of care) tend to have better outcomes than the traditional ones.^21^

### Advantages of the adopted methodology

COFI will be the first natural experiment to compare different approaches to routine mental healthcare provision.

Natural experiments have a number of advantages over randomised controlled trials in health service research.^46–49^

From a practical point of view, the costs related to reorganisation of the mental healthcare services in multiple areas of a country for an experimental trial would not be sustainable or feasible. With a natural experiment design, a high number of patients can be recruited and the effectiveness of different care approaches can be assessed in different areas with no excess treatment costs.

From a scientific point of view, an assessment of routinely provided care avoids the ‘novelty bias’ related to the enthusiasm of patients and clinicians for a newly established way of receiving or providing care.^21^ Patients will be receiving and evaluating standard care instead of a new intervention.

The choice of the sites is very important for a natural experiment. The clinical sites recruited reflected a wide range of geographical areas. The five participating countries have both care approaches as part of their routine mental healthcare provision in different cities or areas of a different city; therefore, the comparison will not be biased by within-country variables. Potential clustering of outcomes will be explored considering random effects at a hospital level.

The countries selected for COFI offer a wide variety of traditions, policy models and funding mechanisms of mental healthcare. They are located in different areas of Europe and share commonalities in sociopolitical characteristics as well as practice and organisation of mental healthcare with non-included neighbouring countries. Therefore, it is expected that COFI findings can be generalisable to a larger number of countries in Europe than those included in the study.

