## Design and methods

### Study design

COFI is a natural experiment, prospectively following up for 1 year patients who, at the point of entry in the study, are hospitalised within care services adopting either a ‘specialisation’ or ‘personal continuity’ approach. Participating sites are located in five countries (Belgium, Germany, Italy, Poland and UK). In these countries both approaches are present, although practice, traditions, policies and funding of mental healthcare vary significantly.

Each included patient can only be treated within either a ‘specialisation’ or ‘personal continuity’ care approach, and the exposure of patients to either approach is outside of the control of investigators and hence, naturalistic. Allocation to either model is based on the given organisation of care in a defined geographical area (UK, Italy), on a clinical decision and patients’ choice (Belgium, Poland), or on insurance arrangements (Germany).

The methodology of a natural experiment has the main advantage of allowing comparisons of the two approaches without altering already established routine provision of care.

However, this implies that no randomised allocation of patients to different approaches is possible. Given the risk of bias associated with a non-randomised design, adjustment for potential confounders is of paramount importance.^26^ In our study, potential confounders will be adjusted for by exploring random effects at a hospital level which will provide an estimate of the potential variability of practice and outcomes both within countries and in different services within the countries.

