### Settings

COFI is coordinated by the Unit for Social and Community Psychiatry, Queen Mary University of London (QMUL). QMUL is responsible for data collection in 11 provider organisations, that is, National Health Service (NHS) Trusts, in the UK as well as for overall project management.

Collaborating academic centres which are responsible for data collection in the remaining four countries are: (1) University of Louvain (Belgium); (2) Technische Universität Dresden (Germany); (3) University of Verona (Italy); (4) Institute of Psychiatry and Neurology of Warsaw (Poland). In each country, at least four hospitals in which a ‘specialisation approach’ is used and four hospitals in which a ‘personal continuity approach’ is used will be included in data collection. In Belgium, Germany and Poland, patients treated under ‘specialisation’ and ‘personal continuity’ of care approaches can be admitted to the same hospital as organisation of care is based on insurance arrangements or clinical decisions for the individual patients.

The hospitals in which patients are recruited are spread throughout the participating countries (see figure 2).

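### The claim of no within-country bias contradicts the patient-by-patient allocation described for Belgium, Germany and Poland, where selection left after covariate adjustment can enter the pooled effect

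*Protocol article*

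**What the plan says.** The no-bias statement is in the protocol article, Discussion, Advantages of the adopted methodology. For all five countries together it says that both approaches exist "in different cities or areas of a different city; therefore, the comparison will not be biased by within-country variables".

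The methods sections describe two ways in which patients come to an approach:

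- **UK and Italy.** Study design says allocation is "based on the given organisation of care in a defined geographical area (UK, Italy"). All patients of a provider get the same approach.
- **Belgium, Germany and Poland.** Study design says allocation rests "on a clinical decision and patients’ choice (Belgium, Poland), or on insurance arrangements (Germany"). Settings says that both approaches can run in one hospital because "organisation of care is based on insurance arrangements or clinical decisions for the individual patients". Establishing exposure adds that placement is decided by insurance (Germany) and/or "by a mental health team decision in which the patient may or may not be involved (Belgium, Poland and Germany"), and that "a patient is included in either group based on the primary hospital clinician report at discharge in Belgium, Poland and Germany".

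On analysis, the section on clinical and social outcomes states: "Mixed effects models with an unstructured variance matrix will be used to assess differences in the primary outcome (rehospitalisation"). Random effects are for hospitals or, in the three countries, for approach clusters within hospital. The fixed covariates are "Age, gender, diagnostic group, whether or not a patient has been previously admitted, severity of illness at baseline, social situation (SIX score) and formal status" at baseline. Seven exploratory subgroup interactions are listed, all on patient characteristics. Neither list contains country or allocation mechanism.

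**The concern.** The Discussion sentence is an inference: separate places, therefore no within-country bias. Its premise does not describe three of the five countries. Where a team, a patient or an insurance arrangement decides who gets which approach inside one hospital, placement is itself a within-country variable, and it may be related to readmission risk. In the UK and Italy the premise holds but the conclusion still does not follow, because areas and providers within a country can differ in ways that affect readmission.

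Study design names hospital-level random effects as the means of adjusting for confounders. These account for correlated outcomes and for variation between hospitals. They do not balance the two groups of patients within a hospital, and a random effect for each approach cluster within a hospital does not either. The planned selection-bias check compares the recruited sample with all admitted patients, not one approach with the other.

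The study intends policy recommendations to national governments. Part of any pooled difference could reflect who is placed under each approach, and the published text would tell readers that this source of bias is absent.

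**Working it through.** **1. The plan's own sample size.** Sample size determination gives 27.5% against 32.5%, 80% power and a 5% level (taken as two-sided, 1:1).

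- Without continuity correction: [1.96·√(2·0.30·0.70) + 0.8416·√(0.275·0.725 + 0.325·0.675)]² / 0.05² = 1318 per group, 2636 in total.
- With continuity correction: 1358 per group, 2716 in total, as stated.
- Design effect: 1 + 127 × 0.007 = 1.889, stated as 1.90. Then 2716 × 1.90 = 5160, against the stated 5162.

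These figures reproduce and are not in dispute.

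**2. Share of patients placed individually.** At 1200 per country, Belgium, Germany and Poland contribute 3600 of 6000, or 60%.

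**3. How residual selection passes into the pooled effect.** Let b be the shift in the readmission difference, in those three countries, that the covariates do not remove. With equal country sizes and the same design effect throughout, the pooled shift is 0.6 × b. After 15% drop-out, 6000 × 0.85 = 5100 are analysed, and at 30% readmission with an even split

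SE(pooled) = 2·√(0.21 × 1.889 / 5100) = 1.76 points.

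With no true effect, the chance of a significant result is Φ(0.6b/SE − 1.96) + Φ(−0.6b/SE − 1.96). The documents give no value for b, so these are assumed values to show the range:

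| b (points) | pooled shift (points) | chance of p < 0.05 |
|---|---|---|
| 0 | 0 | 5% |
| 2 | 1.2 | 10% |
| 3 | 1.8 | 18% |
| 5 | 3.0 | 40% |
| 8.3 | 5.0 | 81% |

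The last row is 5 / 0.6 = 8.3, the residual shift needed to produce the full target difference.

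**4. What a split by mechanism could show.** Same inputs, with m = 128 in both sets:

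- UK and Italy, n = 2040: SE = 2·√(0.21 × 1.889 / 2040) = 2.79 points; 95% interval ± 5.5; power for a 5-point effect about 43%.
- Belgium, Germany and Poland, n = 3060: SE = 2·√(0.21 × 1.889 / 3060) = 2.28 points; 95% interval ± 4.5; power about 59%.
- Contrast: SE = √(2.79² + 2.28²) = 3.60 points. The smallest contrast detectable with 80% power is 2.80 × 3.60, about 10 points. Power for a contrast of 8.3 points is about 64%.

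If the approach clusters within hospital were half the size (m = 64, assumed), the design effect in the three countries would be 1 + 63 × 0.007 = 1.441, their SE 2·√(0.21 × 1.441 / 3060) = 1.99, and the contrast SE √(2.79² + 1.99²) = 3.43. The conclusion is the same.

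**5. Allocation in Germany, side by side.**

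- Study design: insurance arrangements only.
- Settings: insurance arrangements or clinical decisions, for the three countries together.
- Establishing exposure: insurance arrangements and/or a team decision.

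An administrative rule and a clinical judgement carry different selection, so the difference matters for interpretation.

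**The case against.** The strongest reply has four parts.

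- **The bias is conceded elsewhere.** The strengths and limitations box and Study design both say that patients are not randomised. Study design also acknowledges a risk of bias, and the mechanisms are set out country by country. This stands. A reader might infer that the plan hides the selection or would let it act unseen; the documents do not support that.
- **Much of the obvious confounding is adjusted for.** Severity, previous admission, diagnosis, social situation and formal status bear directly on need. This also stands. The concern is only what remains after adjustment, for example insurance type, patient preference and clinician judgement. It is tempting to say that a pooled difference could come wholly from the three countries, but no passage shows how placement relates to readmission risk, and the values of b above are assumptions.
- **Heterogeneity analyses may be in an unseen analysis plan.** They may, so a missing interaction is not counted here as an error in itself. No analysis plan can make the Discussion sentence true, however.
- **The sentence is discussion prose.** It may be a loose version of the nearby claim that coexistence within countries avoids confounding by country. As written, though, it speaks of within-country variables, which is a different claim.

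A further temptation is to treat agreement between the two sets of countries as proof that selection is absent. Potential challenges rules this out. The UK and Italy have continuous electronic records, while the other three rely on phone interviews with attrition possibly above 15%. Mechanism therefore coincides with country set, outcome ascertainment and attrition, and agreement would not exclude area-level bias either.

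**Conclusion.** The point holds in a limited form. The no-bias sentence is contradicted by Study design, Settings and Establishing exposure for three countries that make up about 60% of the planned sample, and it does not follow for the other two. The planned random effects do not supply the missing protection. Selection beyond the seven covariates can enter the pooled estimate at roughly 0.6 of its size, and area differences remain possible in the UK and Italy. Neither amount can be read from the documents.

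The figures assume equal country sizes, an even split between approaches, 30% readmission, the plan's ICC of 0.007, m = 128 and 15% drop-out in both sets. The plan itself expects drop-out to differ between the sets, so the set-specific standard errors are approximate. A split by mechanism would be informative but imprecise, and a difference between sets could not be attributed to selection alone.

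**What to change.** 1. Withdraw the no-bias sentence and state the two biases that remain: differences between areas in the UK and Italy; and, in Belgium, Germany and Poland, selection of individual patients that the baseline covariates do not capture.
2. Reconcile the three descriptions of allocation in Germany.
3. Prespecify an approach-by-allocation-mechanism interaction for readmission (UK and Italy against Belgium, Germany and Poland). Report the adjusted effect with its 95% confidence interval for each set beside the pooled effect.
4. Label this a sensitivity check. State that the contrast has a standard error of about 3.6 points under the plan's assumptions, and that disagreement may also reflect country, outcome ascertainment or attrition.
5. Do not make interpretation depend on the two estimates agreeing in direction. If the effect were absent in the UK and Italy, their estimate would fall on the same side as the other set about half the time by chance, so the rule would pass a biased result about as often as not.

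The cost is one interaction term, two further estimates from data already being collected, and a few sentences of text. The pooled analysis and the sample size are unchanged. The drawback is that the set-specific intervals, about ± 5.5 and ± 4.5 points, are wider than the pooled one at 1.96 × 1.76, about ± 3.5 points.
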